##### E-learning modules

Two e-learning modules were developed on the SOFIA learning platform (ACCO, Leuven, Belgium). This platform includes various didactic functionalities (text, audio, video) to convey information. Furthermore, it allows the integration of inquiries or free text fields for participants to reflect on personal experiences, needs or concerns.

The first e-learning module addresses the risks related to alcohol use, and the current guidelines. In addition, tools for EIBI on alcohol consumption will be presented. The focus here is on how to start a conversation on alcohol use, how to use the Alcohol Use Disorder Identification Test(−Consumption) (AUDIT(−C)), and how provide simple or brief advise to patients according to the possibilities. This first e-learning module was estimated to take 50 min to complete.

The second e-learning will elaborate on how to provide a brief intervention, how to facilitate referral and how to deal with heavy alcohol use or dependence. The importance of a well-defined action plan regarding practice management will be discussed. This e-learning module was estimated to take 30 min to complete.

##### Livestream sessions

Two online interactive training sessions, 90 min each, will be organised via ZOOM (Zoom Video Communications Inc., CA, USA). Both training sessions will proceed on the concordant e-learning modules and are structured by means of a slideshow. During these sessions, emphasis lies on practical exercises and on sharing experiences, problems and solutions. In order to facilitate these sessions, breakout rooms will be used to divide the GPs into smaller virtual groups where they can practise the application of EIBI through role playing and discuss it among themselves. GPs will be grouped based on their practice organisation to allow group discussions in which all GPs can participate equally while also creating a more personalised setting. Attention will be given to possible choices in the task definition, practice organization, and collaborative care, in accordance with the TDF and BCW.

The booster training sessions will start with GPs sharing their personal experiences, perceived barriers and facilitators concerning EIBI delivery. Participants will be grouped according to their similarities in TDF domains and their EIBI activity. This will be measured by preceding online inquiries and by evaluating the use of the e-forms respectively. The content of these sessions will be adapted based on the responses of the TDF inquiries [12, 34]. GPs will be stimulated to discuss problems met with experienced trainers and to share good practices with the group.

### Support

The GPs will receive ongoing support through individual feedback concerning their EIBI-performance, their expressed needs and views, and practice organisation. This on 3-monthly intervals (Table 1). This well-established, evidence-based strategy for quality assurance [19] will be implemented only in the two T&S areas (municipality 1 and 2).

#### Community actions

In their Phase IV study, the WHO suggests that an additional beneficial impact of CA on EIBI uptake is possible, although conclusive empirical data is not yet available [20]. Therefore, we will assess the effect of tailored T&S in a municipality with CA to reframe public and professional views on alcohol (municipality 1) and compare it to municipalities without CA (municipality 2 and 3). These actions will include, but will not be limited to, mass media information campaigns, awareness-raising activities and local neighbourhood mediated actions.

##### Neighbourhood-mediated actions

Neighbourhood-mediated actions will be organised to address the community’s need to initiate the discussion on alcohol outside the clinical setting [35]. The content of these actions will be customised to the neighbourhood’s needs and concerns and presented by local community champions. These champions are locally acknowledged key people in the communities capable of enabling a cultural shift in favour of the wanted behaviour by promoting important values of the intervention [36, 37]. The research team will provide the needed scientific support and means to organise the actions. Examples of such actions will include debates at community centres, mocktail workshops with informative panels, information sessions or a drink-pouring exercise [38].

##### Mass media

The aim of this mass media campaign is trifold [35]. First, it will address individuals’ behaviour towards alcohol use by increasing knowledge on alcohol-related harms and by creating awareness one’s alcohol consumption. Second, this campaign will motivate the community to discuss alcohol use with their GP. Third, it will support neighbourhood-mediated actions. Various means of mass communication including printed-, broadcast- and social media will be used to convey these messages.

### Timeline

The intervention phase commenced in January 2021 with the recruitment of GPs. Recruitment is spread over 4 months with 1 month difference in the three areas. The study will run for 18 months after baseline assessment (Fig. 1).

### Statistical methods

#### Sample size estimation

The primary research question, driving the sample size calculation, is whether the provision of tailored T&S to GPs alone or in combination with CAs will increase the early identification of hazardous and harmful alcohol use among consulting adults in general practices.

The study is powered to detect a statistically significant difference in the cumulative screening rate over the 18-month intervention period. Based on the results of the ODHIN study, we expect the intervention (tailored training and support to GPs) to achieve a rate of screening that is at least 12% or a doubling of the actual screening rate that is assumed [39]. For an alpha of 0.05 and 80% power, a total sample size of 1167 adult patients (389 in each group) is estimated.

To account for a clustering effect at the primary care practice level, with an intra-cluster correlation coefficient (ICC) set at 0.03, based on the findings of the ODHIN study, and a mean cluster size of 2256 patients (2.35 GPs per practice each seeing 960 adult patients per 3 months), the number of patients required was multiplied by 68.65 corresponding to the cluster design effect (DE = 1 + ICC (size of the cluster-1)). Thus, the final sample will consist of 80.115 patients (26.705 per arm), and 84 GPs are needed (28 in each region).

Although conclusive empirical data on the impact of CA is not available, a combined intervention-effect of the mean practice screening rate was set at 20%. This was based on practical experiences and international discussions with other researchers in the field and relates to the needed effect size to consider CA worthwhile. To detect a difference in screening rate of 8% between municipality 1 and municipality 2, we would have a power of 87%.

### Statistical analysis plan

Baseline characteristics of the participating GP population will be compared for the 3 arms including practice (practice size, multidisciplinary practice, practice management EIBI) and GP characteristics (gender, training background, and TDF domains).

The primary outcome of the study will be the proportion of consulting adult patients screened, measured over the 18-month intervention period. The primary endpoint will be analysed according to the intention-to-treat approach. Therefore, linear regression will be used for our data analysis with early identification rates over the 18-month intervention period as a continuous outcome and the intervention group as a factor. Adding a random effect in the model will deal with clustering by general practice. The group effect will be reported as a relative risk with a 95% confidence interval. Secondary outcomes will be analysed similarly.

Subgroup analysis will allow to investigate how the primary outcome behaves in function of covariates. Here, the hierarchical nature of the data and characteristics at different hierarchy levels (i.e. characteristics of the GPs, characteristics of the practices) will be taken into consideration. Participants will be compared for primary and secondary outcomes according to changes in views as measured by TDF domains and practice organisation, taking into account the presence of CAs.

A distinction between active GP participants from less active GP participants will be made by listing those who used the AUDIT(−C) e-forms at least once versus those who did not use these forms.

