### Outcomes

The primary outcome comprises the overall early identification-rates of GPs during the 18-month period, specified per municipality. This is the proportion of the consulted adult patients (> 18 years) attending general practice for any reason, which were questioned about their alcohol consumption over an 18-months period at area level.

The early identification rates will be measured as follows:
**Numerator:** Patients (> 18 years) attending general practice for any reason who are questioned about their alcohol consumption during the study period of 18 months per area.**Denominator:** Number of unique patients (> 18 years) attending general practice during the 18 months study period per area.

Secondary outcomes will be related to personal views, as measured using the TDF domains, to practice organisation and to provided support. These secondary outcomes comprise (a) the cumulative early identification rates and (b) the cumulative brief intervention rates.

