##### Online GP enquiry

Four times a year, GPs will receive an online questionnaire to (Table 1):
Identify positive and negative experiencesAssess role security and therapeutic commitment of the participating GPs using the Short version of the Alcohol Attitudes Problems Perception Questionnaire (SAAPPQ) [41].Measure views based on TDF domains in relation to knowledge and skills for EIBI, personal priority setting, peer’s views, motivation, readiness for change, and emotional coping.Identify T&S needs.Obtain insights into created opportunities and changes in practice approach (e.g., case findings versus screening, targeted or universal, application of task delegation, waiting room materials, or facilitating internet access).

Every three months, an integrated dataset, linked with NHS-codes, will be created containing:
Absolute number of EIBI per age group, gender, area, and GPClinical audit data of the adult population stratified for gender and age-groups per area and GPGPs characteristics, views, experiences, practice management and needs per area and GPT&S received per GP in the intervention areas

The data will be presented as feedback to the GPs for benchmarking by area in municipality 1 and 2. In order to compare primary and secondary outcome measures, at patient counts per area level, EIBI rates will be grouped per area. Furthermore, a comparison will be made between age groups, gender, and co-morbidity since the start of the study.

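### The primary analysis fits a linear model to rates, which yields a rate difference, but promises a relative risk, and the unit of analysis is not consistent between sections

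*Protocol article*

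**What the plan says.** The Statistical analysis plan section of the protocol article defines the outcome as a patient proportion: "The primary outcome of the study will be the proportion of consulting adult patients screened, measured over the 18-month intervention period". It then names the model, "linear regression will be used for our data analysis with early identification rates over the 18-month intervention period as a continuous outcome", with intervention group as a factor. On clustering it says: "Adding a random effect in the model will deal with clustering by general practice". On the effect measure it says: "The group effect will be reported as a relative risk with a 95% confidence interval". Secondary outcomes are to be handled in the same way.

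The Outcomes section sets the level of the outcome differently: "The primary outcome comprises the overall early identification-rates of GPs during the 18-month period, specified per municipality". Numerator and denominator are both counted by area; the denominator is the number of unique adults "attending general practice during the 18 months study period per area". The Online GP enquiry section, on comparing primary and secondary outcomes, says: "at patient counts per area level, EIBI rates will be grouped per area".

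**The concern.** There are two mismatches in the current text.

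- **Model and effect measure.** A linear regression of a rate on arm has a rate difference as its group coefficient. The plan promises a ratio with a confidence interval and does not say how to get from one to the other. Analysts could choose different routes and different intervals and all claim to follow the plan.
- **Unit of analysis.** The outcome is one rate per municipality, but the model carries a practice random effect. The text never says whether a row of data is an area, a practice, a GP, a period or a patient. The choice also moves the target: an unweighted model of GP rates estimates the mean GP rate, which differs from the proportion of patients screened when GPs see different numbers of patients.

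A secondary matter is precision. The planning rates of 6%, 12% and 20% imply different variances, and an ordinary linear model assumes a single one.

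**Working it through.** **1. The plan's own figures.** Inputs from Sample size estimation: 12% vs 6% (the 6% follows from the stated doubling), alpha 0.05 (taken as two-sided), power 80%, ICC 0.03, cluster size 2256.

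- Two proportions without continuity correction: n = [1.96·√(2·0.09·0.91) + 0.842·√(0.06·0.94 + 0.12·0.88)]² / 0.06² = 356. With continuity correction: 389 per group, as stated.
- Design effect: 1 + 0.03·2255 = 68.65. Then 389·68.65 = 26,705 per arm and 1167·68.65 = 80,115 in total, as stated.
- 26,705/960 = 27.8, so 28 GPs per arm; 26,705/2256 = 11.8, so about 12 practices per arm.
- Power for 20% vs 12% with 389 per group: 86.2%, against the stated 87%.

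These figures come from a formula for two proportions, so changing the analysis model does not alter the planned number.

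**2. Scale.** The stated model's coefficient and the promised measure are different quantities:

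| Contrast | Coefficient (points) | Relative risk |
|---|---|---|
| 12% vs 6% | 6 | 0.12/0.06 = 2.00 |
| 20% vs 12% | 8 | 0.20/0.12 = 1.67 |
| 20% vs 6% | 14 | 0.20/0.06 = 3.33 |

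**3. Unit.** Each possible row, set against the stated model:

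- Area: 3 observations minus 3 group parameters = 0 residual degrees of freedom. No standard error and no practice effect can be estimated.
- Practice: with one rate per practice, a practice random intercept cannot be separated from the residual in an ordinary linear model.
- GP, period or patient: the stated random effect can be fitted, but the analysis section names none of these.

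**4. Precision, if a common variance is used.** Assumptions: 12 practices per arm, one rate per practice, 2256 patients each, ICC 0.03 in every arm, beta-binomial data. The variance of a practice rate is 0.03·p(1−p) + 0.97·p(1−p)/2256. The SD is 4.1 points at 6%, 5.7 at 12% and 7.0 at 20%.

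- Common variance: the mean of the three is 0.003266, so SE = √(2·0.003266/12) = 2.33 points for every contrast.
- True SE, 12% vs 6%: √((0.001716 + 0.003213)/12) = 2.03 points, so the common-variance SE is about 15% too large.
- True SE, 20% vs 12%: √((0.004869 + 0.003213)/12) = 2.60 points, so the common-variance SE is about 10% too small.

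Coverage of 95% intervals in 20,000 simulated trials (relative-risk intervals by the delta method):

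| Contrast | Difference, common variance | Relative risk, common variance | Relative risk, separate variances |
|---|---|---|---|
| 12% vs 6% | 97.4% | 98.7% | 94.3% |
| 20% vs 12% | 92.2% | 94.1% | 94.6% |
| 20% vs 6% | 94.7% | 98.2% | 93.9% |

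The common-variance test of 12% vs 6% rejected in 73.7% of runs. Type I error was 4.8% with all three arms at 6%, and 1.4% for 6% vs 6% when the third arm was at 20%.

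**The case against.** The strongest reply is that the plan can be made to work. A ratio of fitted group means is a relative risk. In the simulation its medians were 2.01, 1.67 and 3.37 against true values of 2.00, 1.67 and 3.33, and a delta-method or bootstrap interval is available. A coherent unit can also be read in: the Outcomes section speaks of GP rates, the audit and the three-monthly dataset hold data by GP, and practices average 2.35 GPs, so GP rates nested in practice could be fitted. Variance structure and weighting are details that an article may leave to the full plan.

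Much of this stands, and it rules out three stronger readings that a reader might infer.

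- That the model cannot yield a relative risk. It can, through a further step; the text simply does not state that step or its interval.
- That the standard errors are wrong. This depends on the unstated unit and on a common variance. The figures above use practice-level rows, which are not quite the stated model. For 20% vs 12%, relative-risk coverage is near nominal even with a common variance.
- That pooled area counts will be compared with no allowance for clustering, understating the SE by √68.65 = 8.3 times. The practice random effect in the analysis section excludes this, and the sentence on grouping rates per area stands under data collection.

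The reply does not remove the mismatch itself. The text names a model and an effect measure that do not belong together, and it defines the outcome at a level that cannot carry the random effect. These are contradictions in what is written, not details left for later.

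**Conclusion.** The point holds as a specification error in the primary analysis, and the secondary outcomes inherit it. As written, the model gives a rate difference (6 or 8 points on the planning rates) where a relative risk (2.00 or 1.67) is promised. The per-area outcome, with zero residual degrees of freedom, conflicts with a random effect that needs rows below practice level.

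The effect on precision is conditional and moderate. With practice-level rates, 12 practices per arm, a constant ICC of 0.03 and one common variance, coverage for the rate difference is about 97% for 12% vs 6% and about 92% for 20% vs 12%. Type I error is near nominal when all rates are equal. Separate variances by arm bring relative-risk coverage to about 94 to 95%. The planned sample size is unaffected.

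**What to change.** Make three changes in the analysis section before the data are analysed.

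1. **Name the unit**: for each GP, the number of adults screened out of unique attending adults over 18 months, with GPs nested in practice. Say how a patient seen by two GPs of the same practice is counted.
2. **Match model to measure.** Replace the linear model with one that gives the relative risk directly: a log-link binomial model, or a Poisson model with robust variance and the log denominator as offset. Enter municipality as a three-level factor, with a practice random effect or a practice-clustered variance with small-sample correction. The three-level factor supplies municipality 1 against 2 and against 3, both of which the Community actions section sets out to compare. Alternatively, keep the linear model, report the rate difference and let variances differ by arm.
3. **State that pooled area rates are descriptive**, and align the Outcomes and Online GP enquiry sections with this.

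The cost is mostly wording, with one thing to confirm first. The Clinical audit data section lists patients seen in each past 3 months and patients registered. Neither is the number of unique attenders over 18 months, and quarterly counts cannot be summed to it because a patient may attend in several quarters. If that count per GP cannot be extracted from the records, the change needs an extra audit query as well as new text.

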## Methods

### Study design and setting

The PINO-study consists of a quasi-experimental three-arm implementation study in three comparable medium-sized Flemish (Belgium) municipalities [28]. All three municipalities have a multicultural population with around 80,000 to 100,000 inhabitants. In addition, they are all marked by a large student population due to the presence of universities or university colleges [28].

#### Municipality 1

Intervention area where GPs receive T&S embedded within a community mobilisation program.

#### Municipality 2

Intervention area where GPs receive T&S without CA.

#### Municipality 3

Support As Usual (SAU) area where GPs receive a minimal intervention that comprises an overview of the current guidelines and knowledge.

During an 18-month implementation period, GPs in the T&S area’s will receive personalised support linked to an online evaluation of their needs, views, practice organisation and EIBI-performance. This on a three-monthly base (Fig. 1).

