##### Clinical audit data

For every participating GP, the following data will be collected through a clinical audit of their EHR (Table 1):
The number of patients seen per practice and GP over the past 3 months at 0, 3, 6, 9, 12, 15 and 18 months;The total number of unique patients registered with a GP or practice at 0, 12 and 18 months

GPs send clinical audit data to a double secured server at the Academic Centre for General Practice (ACHG), as authorized in the ICF. The data remain linked to the National Health Services Coding of the consulted GP (NHS-Code).

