## Discussion

The strength of this study is the combination of training and interactive support, tailored to a theory-based implementation strategy (TDF and BCW) and measured during the implementation process. PINO addresses both in- and external barriers and facilitators. This will increase GPs’ experience according to their daily practice and develop good experiences by learning from less successful ones to obtain sustained behavioural and practice change. What also distinguishes PINO from other studies is the inclusion of CAs and evaluating their added value on the delivery of EIBI in general practice.

The PINO-project has some potential limitations. There is a possibility for selection bias within the recruitment of GPs. Highly motivated GPs are more likely to participate compared to more sceptical or less motivated GPs. Nonetheless, a quasi-experimental design is the right fit for this project due to its pragmatic character and the strong external validity [42]. In order to minimize potential bias, necessary precaution was taken when designing the study (e.g., including a control area, using appropriate analytical techniques). Additionally, GPs may address the subject of alcohol consumption but forget to register it in their EHR. It is also possible that GPs remember to register, but do not fill in the e-form correctly. These problems should however occur less in the cities where GPs receive T&S. These concerns have been taken into account while designing this study by integrating both e-forms as well as clinical auditing of the EHR. The e-form provides GPs the opportunity to discuss and systematically record how much alcohol their patients use. Another matter to consider is the possibility that data collection is incomplete due to technical errors, which will be take into account during the analysis.

Nevertheless, the strengths of this study outweigh its limitations. PINO is based on theoretical models of implementation and includes theory-based interventions to promote the desired behaviour. It addresses the attitudes of GPs towards working with at-risk drinkers, and it tailors its program to their views and needs.

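### The primary model of a non-randomised comparison leaves out the baseline GP and practice covariates that the study already collects

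*Protocol article*

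**What the plan says.** Under Study design and setting: "The PINO-study consists of a quasi-experimental three-arm implementation study in three comparable medium-sized Flemish (Belgium) municipalities". Each municipality is one arm. Under Recruitment and eligibility criteria, all GPs in the three areas are approached and those who agree sign a consent form.

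Under Statistical analysis plan, the primary analysis is a linear regression "with early identification rates over the 18-month intervention period as a continuous outcome and the intervention group as a factor". One further element is named: "Adding a random effect in the model will deal with clustering by general practice". The group effect is to be reported as a relative risk with a 95% confidence interval.

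The same section gives covariates two other roles. First, "Baseline characteristics of the participating GP population will be compared for the 3 arms"; the characteristics listed are the size of the practice, whether it is multidisciplinary, how it manages EIBI, and the GP's gender, training background and TDF domains. Second, "Subgroup analysis will allow to investigate how the primary outcome behaves in function of covariates".

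The Discussion accepts a risk of selection bias: "Highly motivated GPs are more likely to participate compared to more sceptical or less motivated GPs". It says precautions were taken ("e.g., including a control area, using appropriate analytical techniques").

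**The concern.** A model with group as its only fixed effect is defensible when randomisation balances the arms in expectation. Nothing does that here. If the practices that volunteer in one municipality are larger, more often multidisciplinary or already organised for EIBI, and such practices screen more, the difference appears in the estimated effect of training and support or of community actions.

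The random effect does not help with this. It widens the standard error to allow for clustering within practices and leaves any shift in the arm means where it was. Comparing baseline characteristics may reveal an imbalance but does not correct the estimate. Part of the subgroup work relates outcomes to changes in TDF views, which arise after baseline and cannot repair baseline confounding.

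The Background itself reports that training raises EIBI rates more among confident and committed GPs, so the protocol regards such traits as relevant to the outcome. Yet the analytical techniques that the Discussion offers as protection do not appear in the primary model.

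**Working it through.** **Inputs.** From Sample size estimation: 12% screened with training and support, described as a doubling, so 6% without; alpha 0.05; power 80%; ICC 0.03; mean cluster size 2256; 389 patients per group before clustering. No document gives a baseline imbalance between arms, so that is an assumption below.

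**1. The plan's own figures reproduce.**
- Two-sided test of 6% against 12%, uncorrected: n = [1.96 × √(2 × 0.09 × 0.91) + 0.8416 × √(0.06 × 0.94 + 0.12 × 0.88)]² / 0.06² = 356 per group. With continuity correction, n = 389, the stated figure.
- Design effect = 1 + 0.03 × (2256 − 1) = 68.65.
- 389 × 68.65 = 26,705 per arm; 1167 × 68.65 = 80,115 in total.
- 26,705 / 960 = 27.8, hence 28 GPs per arm.

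The sample size is not in dispute. It is used only to scale the problem.

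**2. Practices per arm.** 26,705 / 2256 = 11.8, about 12.

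**3. Standard error of an arm difference.** Between-practice SD = √(ICC × p × (1 − p)).
- p = 6%: √(0.03 × 0.06 × 0.94) = 4.1 points; SE = 4.1 × √(2/12) = 1.7 points.
- p = 9% (midway between 6% and 12%): √(0.03 × 0.09 × 0.91) = 5.0 points; SE = 5.0 × √(2/12) = 2.0 points.

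Sampling error within practices is left out; it is about 1/68.65, or 1.5%, of the variance.

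**4. Effect of an assumed imbalance b when the intervention does nothing.** P(reject) = 1 − Φ(1.96 − b/SE) + Φ(−1.96 − b/SE). The last column adds b to a 6% reference rate; the planned relative risk is 12/6 = 2.

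| Assumed imbalance | Reject, SE 1.7 | Reject, SE 2.0 | Spurious relative risk |
|---|---|---|---|
| 0 points | 5.0% | 5.0% | 1.00 |
| 1 point | 9.2% | 7.8% | 7/6 = 1.17 |
| 2 points | 22.2% | 16.7% | 8/6 = 1.33 |
| 3 points | 43.1% | 31.7% | 9/6 = 1.50 |

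**5. Room for covariates.** About 3 × 12 = 36 practices, less 3 arm means, leaves 33 degrees of freedom at practice level. Four covariate terms leave 29.

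**The case against.** The strongest reply has three parts. The municipalities were chosen to be comparable and recruitment follows the same procedure in each, so volunteering may select equally everywhere. Covariates are not ignored, since the subgroup paragraph looks at the primary outcome as a function of GP and practice characteristics and respects the hierarchy. And a condensed article may leave the covariate list to a fuller plan.

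The first part limits what can be claimed about size, but similarity of the municipalities does not show that the volunteering practices are alike. The second does not meet the point, because the relative risk named as primary comes from the model with group alone. On the third, the exact list could well be left to another document. But the article does not merely omit a list: it states the fixed part of the primary model and assigns the covariates elsewhere.

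Several stronger readings are tempting, and the documents do not support them.
- A reader might infer that the protocol concedes bias between arms. The Discussion says only that participants are likely to be more motivated than non-participants. Bias in the relative risk needs selection that differs by arm, which is not stated.
- A reader might infer that GPs joined knowing what their own area would receive. The article describes a standard letter and clarifying telephone calls, and does not say this.
- A reader might infer that the month-0 audit yields a baseline screening rate. Its listed items are "The number of patients seen per practice and GP over the past 3 months at 0, 3, 6, 9, 12, 15 and 18 months" and the number of registered patients. Both are denominators. The numerator comes from e-forms that GPs receive only after consent. The Discussion describes EHR auditing as a complement to the e-forms, but no such count is listed, and Table 1 is not shown.
- A reader might take the SAAPPQ as an available baseline covariate. It is administered four times a year, and its timing relative to training cannot be confirmed.

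**Conclusion.** The point stands as a weakness in the stated primary analysis: a non-randomised comparison of volunteering GPs is estimated with group and a practice random effect only, while relevant baseline characteristics are already in hand. Measured imbalance in them passes unadjusted into the primary relative risk.

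The size of the resulting bias is unknown. The rejection rates of roughly 8-9%, 17-22% and 32-43% rest on assumed imbalances of 1, 2 and 3 points, on 12 equally sized practices per arm, on the planned ICC and on a normal reference distribution. They show that an imbalance well below the planned 6-point effect would matter, not that one exists.

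Nor can adjustment make the arms exchangeable. With one municipality per arm, differences between areas cannot be separated from the intervention by any set of GP or practice covariates. What adjustment can do is reduce the measured imbalance among GPs and practices.

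**What to change.** Rewrite the primary model to contain intervention group, a practice random effect and about three or four prespecified terms drawn from the baseline characteristics already listed: practice size, multidisciplinary practice, EIBI practice management, GP gender, training background, and TDF domains reduced to a single score. State that each is measured before training. Choose them on subject-matter grounds, not on observed imbalance, and date the choice, since the research team has access to interim results.

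Standardise or adjust for patient age group and sex. According to Online GP enquiry, both the EIBI counts and the audit data are already broken down by these. Report the unadjusted estimate as secondary.

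Optionally, if the number of adults with a recorded alcohol enquiry before baseline can be extracted from the EHR, enter it as a practice-level covariate. Do not use it for difference-in-differences: EHR entries and e-form records are different instruments, and their difference would mix a change in recording with a change in screening.

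State plainly that adjustment reduces measured GP and practice imbalance but cannot remove municipality differences.

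The cost is a change of wording and up to four of roughly 33 practice-level degrees of freedom, with no new data for the covariates. Only the optional count needs extra work, probably a retrospective extraction, since recruitment began in January 2021 and the article appeared in July 2021.
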